# Randomization

Patients participating in the trial will be assigned a sequential trial number. The computer-generated list of trial numbers is linked to a randomized list with medication numbers, equivalent to 80 batches of indomethacin and 80 batches of placebo. The participating pharmacist will retain the randomization code. This procedure warrants a well-balanced initial randomization. However, a difference in the number of patients will occur when patients are withdrawn from the trial. The number of patients withdrawn from the indomethacin group will provide significant information in the final analysis of the data (“intention to treat”).

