## Side effects

The risk for gastrointestinal side effects related to the use of NSAIDs in elderly people is 20 percent. In patients of 50 years and older, using a high dosage of the NSAID indomethacin and using corticosteroids at the same time, the risk of serious gastrointestinal complications can be 10 times higher, especially during the first three months. To prevent possible gastrointestinal side effects, omeprazol (20 mg once a day) will be prescribed21.

The patient’s discomfort will be small when no inconvenient side effects occur. A (small) discomfort for the patient will be the puncture in order to get blood samples.

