## Measures taken in case of adverse events

An adverse event is any undesirable sign, symptom or medical condition occurring after starting the intake of the trial medication, whether considered drug-related or not. Medical conditions/diseases present before starting the trial medication are only considered adverse events if they worsened after starting the medication.

In case of an adverse event with a possible causal relationship to the use of indomethacin, the medical attendant (e.g. family physician, physician) will discontinue the trial medication. The trial ends, however the trial code will not be broken and the patient’s data will be analyzed. The medical attendant will be asked to report this decision to the investigators as soon as possible.

The medical attendant is allowed to lower the dose of the study medication, in case of a dubious causal relationship between the adverse event and the study medication. The trial code will not be broken and the patient will be considered a normal participator of the trial.

In case of a serious adverse event, the patient’s medical attendant will ask the pharmacist to announce the nature of trial medication. The code will then be broken, the medication will be discontinued and the patient’s data will not be included in the analysis of the final outcome measures. However, the data of patients discontinuing the trial will analyzed according to the “intention to treat” principle.

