# Statistical considerations

## Sample size

For estimation of the required sample size, the following assumptions were made:

- patients deteriorate 5.0 points (SD 7.0) on the ADAS-cog in one year.
- a difference of 3.0 points or more regarding the changes from baseline is considered to be clinically relevant in case indomethacin is tested against placebo.
- power of 80 percent.
- statistical testing will be done one-sided, at a significance level of 0.05.

Based on the above statistical considerations, a total of 67 patients per group will be necessary. Assuming a dropout rate of 20 percent, the total sample size will be 160 patients (80 patients per group).

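### The 80% power in section 12.1 does not match its own dropout rate (64, not 67, remain per group; about 78%), and it makes no allowance for patients who stop treatment but stay in an intention-to-treat comparison

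*Protocol*

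**What the plan says.** Section 12.1 (Sample size) sets the target first of all by relevance: "a difference of 3.0 points or more regarding the changes from baseline is considered to be clinically relevant". For the expected course and its spread it assumes that "patients deteriorate 5.0 points (SD 7.0) on the ADAS-cog in one year". On the test it says that "statistical testing will be done one-sided, at a significance level of 0.05", and the aim is 80% power. From these inputs it derives 67 patients per group. It then adds the dropout allowance: "Assuming a dropout rate of 20 percent, the total sample size will be 160 patients (80 patients per group"). The 3.0 points is the same before and after that step.

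Three other sections describe who is compared:

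- Section 8 (Randomization), with a reference to intention to treat: "The number of patients withdrawn from the indomethacin group will provide significant information in the final analysis of the data".
- Section 10.3 (Measures taken in case of adverse events), followed by the words for intention to treat: "However, the data of patients discontinuing the trial will analyzed according to the". The same section says that patients taken off medication for a possibly related adverse event have their data analysed. It also says that patients unblinded after a serious adverse event are left out of the final outcome analysis.
- Section 12.3 (Statistical methods) compares the ADAS-cog change of every patient between the two groups.

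No section says whether patients who stop are assessed at week 52, or whether the 3.0 points refers to all randomised patients or to patients on treatment.

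**The concern.** Section 12.1 handles dropout in one way only: it adds patients to replace those lost and gives the remainder the full 3.0 points. That suits an analysis in which dropouts have no outcome and drop out of the comparison. Even on those terms, the number remaining does not agree with the stated dropout rate.

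An intention-to-treat comparison that retains patients who stop works differently. A patient in the indomethacin arm who stops early and is still measured does not reduce the number analysed, but may pull the mean difference towards zero. Section 12.1 allows nothing for this.

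What is at stake is how a null result is read. It would be presented as coming from a trial with a 20% chance of missing a 3.0-point effect, when under plausible readings of the protocol that chance lies between about 22% and 30%.

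**Working it through.** **Inputs from section 12.1.** SD 7.0; difference δ = 3.0; one-sided α = 0.05 (z = 1.645); power 80% (z = 0.842); 67 per group before dropout; 20% dropout; 80 per group randomised.

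**Input not in the protocol (assumption).** f, the share of the effect kept at one year by patients who stop. I show f = 0, 0.25, 0.5 and 1.

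**Formulas.**

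- n per group = 2 × [(1.645 + 0.842) × SD / δ]²
- power ≈ Φ(δ / (SD × √(2/n)) − 1.645)
- diluted difference = 3.0 × (0.8 + 0.2f)

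**Step 1: the plan's own figure.** n = 2 × (2.487 × 7.0 / 3.0)² ≈ 67.3. The stated 67 is this value rounded down; rounding up gives 68. At 67 per group the standard error is 7.0 × √(2/67) = 1.209, and power = Φ(2.481 − 1.645) = 79.8% (79.5% by the exact t-test). The base calculation reproduces.

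**Step 2: the dropout step.** 67 × 1.2 = 80.4, which matches the stated 80. But 20% dropout from 80 leaves 80 × 0.8 = 64. Keeping 67 would take 67 / 0.8 = 83.75, so 84 per group. Conversely, 67 of 80 corresponds to a loss of 1 − 67/80 = 16.25%, not 20%. At 64 per group the standard error is 1.237, and power = Φ(2.424 − 1.645) = 78.2% (77.8% by t-test).

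**Step 3: dilution.** Assume all 80 per group are measured and 20% of the indomethacin arm stop. The standard error is 7.0 × √(2/80) = 1.107.

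| Effect kept by stoppers (f) | Difference | Power, normal | Power, t-test |
| --- | --- | --- | --- |
| 0 | 2.40 | 70.0% | 69.6% |
| 0.25 | 2.55 | 74.5% | 74.2% |
| 0.5 | 2.70 | 78.7% | 78.4% |
| 1 (no dilution) | 3.00 | 85.7% | 85.4% |

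**Step 4: break-even.** With 80 per group, 80% power needs a difference of 2.487 × 1.107 = 2.75 (2.76 by t-test). Solving 3.0 × (0.8 + 0.2f) = 2.75 gives f = 0.59 (0.61 by t-test). Stoppers would have to keep about 60% of the effect. If they keep none, restoring 80% power takes 106 per group (difference 2.4, same formula).

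The last row of the table also covers the reading in which 3.0 points is already the all-randomised difference and everyone is measured.

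**The case against.** **The 3.0 points may already be the all-randomised difference.** Section 12.1 calls it the clinically relevant difference and never ties it to patients on treatment. On that reading no dilution is owed, and power with all 80 measured is about 85%. This stands. It means the protocol leaves open even the direction of the error in Step 3. It does not rescue the 80%, which then belongs to neither 80 nor 64 per group.

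**Dropout may really reduce the number analysed.** Section 8 expects group numbers to diverge as patients withdraw. Section 10.3 says the trial ends for a patient stopped for a possibly related adverse event, and the evaluation schedule has no separate off-treatment visit. Week-52 scores may therefore be missing, and adding patients for missing outcomes is ordinary and compatible with intention to treat. This stands too, and is why the allowance should be corrected and not deleted. But the correct number is then 64.

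**About 70% is the low end.** A reader might infer that the power of this trial simply is 70%. The documents do not support that. It requires that a full 20% of the indomethacin arm stop, that they keep none of the effect, and that all are still measured. If later stoppers keep half, the figure is about 78%.

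**The side-effect rate does not settle it.** A reader might also take section 9.4 ("The risk for gastrointestinal side effects related to the use of NSAIDs in elderly people is 20 percent") as showing that at least 20% will stop indomethacin. That figure is a risk of side effects with NSAIDs in general, not a stopping rate, and the same section prescribes omeprazole to prevent them.

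**Some of this belongs in a statistical analysis plan.** Handling of missing data may well be set out there. The power claim and the dropout arithmetic, however, are fixed in section 12.1 itself.

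**Conclusion.** The point holds in a limited form. One part needs no outside assumption: by its own 20%, section 12.1 leaves 64 per group and about 78% power, a shortfall of about two percentage points. The other part is conditional: if patients who stop remain in the comparison and 3.0 points is an on-treatment difference, power runs from about 70% (no effect kept) to 78% (half kept), and reaches 80% only at about 60% kept. If 3.0 points is the all-randomised difference with complete measurement, power is about 85%.

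The results rest on the SD of 7.0, the one-sided 0.05 test that 12.1 presumes, equal groups, and 20% as the stopping rate in the indomethacin arm. The stated 80% is therefore not matched to the described analysis. How far it is off depends on two facts the protocol does not give: what the 3.0 points refers to, and whether patients who stop are measured. The exclusion in section 10.3 of patients unblinded after a serious adverse event leaves the analysis set itself contradictory.

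**What to change.** Leave the 160 patients and the intention-to-treat analysis as they are, and revise section 12.1 as follows:

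1. Name the analysis set the power refers to, and say whether 3.0 points is the difference among all randomised patients or among patients on treatment.
2. Keep the dropout allowance for missing outcomes, but correct it: 20% dropout from 80 leaves 64 per group.
3. Restate power as about 78% if dropouts are only missing, with a range down to about 70% if patients who stop stay in the analysis with no effect kept. If 3.0 points is declared the all-randomised difference, also give about 85% for complete measurement of all 80 per group.
4. Reconcile the analysis set named in 12.1 with the sentence in 10.3 that leaves patients unblinded after a serious adverse event out of the final outcome analysis.

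The cost is rewording, mainly of 12.1, with no change to enrolment. The downside is a less favourable stated power.

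### At the assumed 20% dropout, 80 patients per group leave 64, not the 67 that section 12.1 calls necessary, so one-sided power is about 78% rather than 80%

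*Protocol*

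**What the plan says.** Section 12.1 (Sample size) of the protocol lists its assumptions and two results.

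- Expected course and spread: "patients deteriorate 5.0 points (SD 7.0) on the ADAS-cog in one year".
- Target difference: "a difference of 3.0 points or more regarding the changes from baseline is considered to be clinically relevant".
- Power and test: "power of 80 percent"; "statistical testing will be done one-sided, at a significance level of 0.05".
- Size before dropout: "a total of 67 patients per group will be necessary".
- Size after dropout: "Assuming a dropout rate of 20 percent, the total sample size will be 160 patients (80 patients per group").

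No formula is printed for either step. The total of 160 is used consistently elsewhere: in section 4 (Study design), in section 5.1, in the recruitment plan of section 6.2 (55 + 55 + 50), and in section 8 (Randomization), where the medication list is "equivalent to 80 batches of indomethacin and 80 batches of placebo". The drug supply in section 9.3 also follows from it: 160 × 2 × 365 = 116,800 capsules. No section gives a different dropout rate or says why 80 per group would suffice.

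**The concern.** The section says how many patients per group are needed, what share will be lost, and how many will be randomized. Any two of these fix the third, and the printed third figure does not agree with the other two.

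A dropout allowance should be made by dividing the required number by the fraction expected to remain. Multiplying by one plus the dropout rate takes the percentage of the wrong base and always gives too few patients. The printed 80 is what that multiplication would give.

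At stake is the accuracy of a stated design property. Anyone interpreting a null result will rely on the claim of 80% power with 20% dropout, and the planned 160 patients do not deliver it on the protocol's own assumptions.

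**Working it through.** **Inputs**, all from section 12.1: difference δ = 3.0, SD of the one-year change σ = 7.0, one-sided α = 0.05, power 0.80, dropout d = 0.20, equal groups.

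**Step 1: reproduce the 67.** For two means, n per group = 2 × [σ(z₀.₉₅ + z₀.₈₀)/δ]².

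- 2 × [7.0 × (1.645 + 0.842)/3.0]² = 67.32.

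The stated 67 is reproduced, rounded down. Rounding up gives 68. The difference is trivial: normal-approximation power is 79.8% at 67 and 80.3% at 68.

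**Step 2: apply the dropout allowance.**

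- Dividing by the fraction retained: 67/(1 − 0.20) = 83.75, so 84 per group and 168 in total.
- Multiplying by one plus the rate: 67 × 1.20 = 80.4, which matches the printed 80.
- Starting from 68 instead: 68/0.80 = 85 per group, 170 in total.

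**Step 3: what 80 per group delivers.**

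- Remaining at 20% dropout: 80 × 0.80 = 64 per group, 128 in total, three per group fewer than 67.
- Dropout at which 67 still remain: 1 − 67/80 = 16.25%, or 13 patients per group. For 68 it is 1 − 68/80 = 15%.

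**Step 4: one-sided power for 3.0 points, α = 0.05.** The normal approximation is Φ(δ/[σ√(2/n)] − 1.645).

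At n = 64: 3.0/(7.0 × √(2/64)) = 2.424, and Φ(2.424 − 1.645) = 0.782.

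| Evaluable per group | Normal approximation | Noncentral t |
| --- | --- | --- |
| 64 (80 less 20%) | 78.2% | 77.8% |
| 67 (declared necessary) | 79.8% | 79.5% |
| 68 (67.32 rounded up) | 80.3% | 80.0% |

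The shortfall from 67 to 64 costs about 1.6 points of power by either method.

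**The case against.** **The effect is negligible.** A loss of 1.6 points is well inside the uncertainty of the SD assumption, and section 5.1 describes the 160 as approximate. The first part stands and sets the size of the finding. The second does not repair the text, because section 8 fixes 80 medication batches per arm and section 12.1 prints the calculation as exact.

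**Dropouts may still be analysed.** Sections 8 and 10.3 invoke intention to treat, and section 10.3 says the data of patients stopped for a possibly drug-related event will be analysed. If all 80 per group supplied a week-52 score with no dilution of the effect, one-sided power would be 85.4%. This is a fair limit: 64 is the number remaining only if dropouts contribute no primary-outcome data. But adding patients for dropout makes sense only on that premise, so on the section's own terms 64 is the right number.

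**The multiplication is a guess.** It is an inference, since no formula is shown. The shortfall does not depend on it, because 80 × 0.80 = 64 whichever way 80 was reached.

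A reader might also infer more than the protocol supports:

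- *That side effects alone will use up the 20% allowance.* Section 9.4 says: "The risk for gastrointestinal side effects related to the use of NSAIDs in elderly people is 20 percent". That is a side-effect rate for NSAIDs in elderly people generally, not a dropout rate for this trial. The same section prescribes omeprazole against such effects, and stopping medication under section 10.3 is not the same as losing the patient's data.
- *That power should be judged at dropout well above 20%.* The protocol gives no other rate, so such scenarios would have no source in it.
- *That power is lower still because the test is two-sided.* Section 12.3 names an ANOVA at 0.05 without calling it two-sided, and section 12.1 says one-sided. Whether the two sections agree is a separate question.

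**Conclusion.** The point holds as a small error in a stated design figure. Taken together, 160 patients, 20% dropout and 67 evaluable per group are inconsistent: 64 per group remain, and one-sided power for a 3.0-point difference is about 78% instead of 80%.

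This rests on the protocol's own difference, SD, one-sided level and dropout rate, on equal dropout in the two groups, and on dropouts giving no week-52 ADAS-cog score. To the extent that discontinued patients are still assessed, the loss is smaller. The finding does not show that the trial is materially underpowered, and it does not call for a larger trial.

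**What to change.** Keep 160 patients and correct the last paragraph of section 12.1. It should say that 80 randomized per group leave 64 per group at 20% dropout, with about 78% one-sided power for a 3.0-point difference, and that 67 evaluable per group requires dropout of no more than about 16%. Stating that the calculation counts dropouts as having no week-52 score would make its premise explicit.

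The cost is one reworded paragraph and a slightly less favourable stated power. Restoring 67 evaluable per group at 20% dropout would instead take 168 patients, eight more, and matching changes in sections 4, 5.1, 6.2, 8 and 9.3. A gain of less than two points of power hardly justifies that.

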## Stratification

During the initial randomization there is no use for further stratification. In the final analysis of the results, the indomethacin and placebo group will be compared concerning age, sex, duration and severity of the disease (ADAS-cog score) and Apo E phenotype.

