## Exclusion criteria

- The patient satisfies the NINDS-AIREN criteria for probable vascular dementia, including:
- presence of focal signs on neurological examination consistent with stroke
- evidence of relevant cerebrovascular disease by brain imaging (CT and/or MRI made within two years before the baseline visit)
- A known exaggerated pharmacological sensitivity or allergy to NSAID’s.
- History of peptic ulceration, gastric surgery or gastrointestinal bleeding.
- Current diagnosis of active peptic ulceration.
- Current diagnosis of severe and unstable cardiovascular disease.
- Current diagnosis of renal failure (creatinin > 200 mol/l).
- Advanced, severe and unstable disease of any type, other than Alzheimer’s disease, that may interfere with primary and secondary variable evaluations, including a medical condition which should be expected to progress, recur, or change to such an extent that it may bias the assessment of the clinical or mental status of the patient to a significant degree or put the patient at special risk.
- Intake of any of the following concomitant medications:
- salicylates
- coumarin derivatives
- ACE-inhibitors
- loopdiuretics
- Intake of any of the following concomitant medications more than two months immediately prior or during the study:
- NSAID’s
- systemic corticosteroids
- Intake of any of the following concomitant medications with a possible effect on cognition:
- estrogen
- deprenyl
- vitamin E
- neuroleptics
- anticholinergics

Patients using stable doses of cholinesterase inhibitors were eligible, with the provision that the dose should not be changed during the study. Cholinesterase inhibitors could not be initiated during the study

- Excessive use of alcohol (> 5 units/day)
- The patient is, either alone or with the aid of a caregiver, not able to reliably take the medication.

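### Baseline cholinesterase-inhibitor use is missing from the Section 12.2 between-arm comparison and the Section 12.3 ADAS-cog model, although Section 5.3 admits and restricts stable users

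*Protocol*

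**What the plan says.** Protocol Section 5.3 (Exclusion criteria) has a group of exclusions headed "Intake of any of the following concomitant medications with a possible effect on cognition". Directly after that list comes an allowance: "Patients using stable doses of cholinesterase inhibitors were eligible, with the provision that the dose should not be changed during the study". The next sentence adds: "Cholinesterase inhibitors could not be initiated during the study".

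Section 8 (Randomization) describes a computer-generated list "equivalent to 80 batches of indomethacin and 80 batches of placebo". Section 12.2 (Stratification) states: "During the initial randomization there is no use for further stratification". It goes on to say that in the final analysis "the indomethacin and placebo group will be compared concerning age, sex, duration and severity of the disease (ADAS-cog score) and Apo E phenotype".

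Section 12.3 (Statistical methods) analyses change in ADAS-cog by an analysis of variance with two factors, group and time. No section plans to compare the arms on cholinesterase-inhibitor use or to adjust for it. Medication is recorded at screening (Section 5.6 and Appendix II), and changes in it are asked about at every later contact.

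**The concern.** The protocol controls cholinesterase inhibitors within the patient: stable dose, no change, no start. Those restrictions make sense mainly if the drug could move a cognitive score. Section 5.3 does not say so outright; the reading rests on where the allowance sits and on the restrictions themselves.

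Between the arms there is no matching provision. If users and non-users decline at different rates, a chance excess of users in one arm moves the observed difference in ADAS-cog change, and neither the named comparison nor the stated model takes account of it. If the imbalance were noticed only after unblinding, any adjustment would be post hoc and open to challenge. At stake are a small conditional shift in the primary contrast and a little precision.

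**Working it through.** **Inputs from the protocol.** Section 12.1 gives an SD of one-year change of 7.0, a mean decline of 5.0, a relevant difference of 3.0, a one-sided alpha of 0.05 and 80% power. Sections 5.1 and 8 give 80 patients per arm.

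**The plan's own figure.** n per group = 2 × [7.0 × (1.645 + 0.842) / 3.0]² = 67.3, which agrees with the stated 67. The inputs are therefore read as the plan meant them.

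**Assumptions.** The protocol gives neither the share of users, p, nor the difference in one-year change between users and non-users, d. I take p = 20-50% and d = 0-3 points. The lower end of d matters because the outcome is change from baseline: a constant effect of a stable drug is already in the baseline score, so only a difference in rate of decline counts.

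**Step 1: chance imbalance.** The 95% extreme of the difference in user proportion is 1.96 × √[2p(1−p)/80]:
- p = 20%: 1.96 × 0.0632 = 12.4 percentage points
- p = 30%: 1.96 × 0.0725 = 14.2
- p = 50%: 1.96 × 0.0791 = 15.5

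From the exact hypergeometric distribution, the chance of an imbalance of 10 points or more is 17%, 23% and 27% respectively.

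**Step 2: shift in the contrast.** Shift = imbalance × d, in ADAS-cog points at the 95% extreme:

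| Users | d = 0 | d = 1 | d = 2 | d = 3 |
|---|---|---|---|---|
| 20% | 0 | 0.12 | 0.25 | 0.37 |
| 30% | 0 | 0.14 | 0.28 | 0.43 |
| 50% | 0 | 0.15 | 0.31 | 0.46 |

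The largest value, 0.46, is 15% of the 3.0-point target. The standard error of the contrast is 7.0 × √(2/80) = 1.11, so 0.46 is 0.42 standard errors. If only 64 per arm remain (80 less the assumed 20% dropout), the same corner of the table becomes 1.96 × √(2 × 0.25/64) × 3 = 0.52.

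**Step 3: precision.** If users belong to the population behind the SD of 7.0, use explains p(1−p)d²/49 of the variance. A model term then multiplies the standard error by √(1 − share). The reduction in standard error is:

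| Users | d = 0 | d = 1 | d = 2 | d = 3 |
|---|---|---|---|---|
| 20% | 0% | 0.2% | 0.7% | 1.5% |
| 30% | 0% | 0.2% | 0.9% | 1.9% |
| 50% | 0% | 0.3% | 1.0% | 2.3% |

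The largest share is 0.25 × 9/49 = 4.6%, which gives 1 − √0.954 = 2.3%.

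**The case against.** The case against is strong, and most of it stands.

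- **Randomisation is valid as planned.** A reader might infer that Section 12.2 is wrong to reject stratification. It is not. Simple 1:1 allocation of 160 patients balances cholinesterase-inhibitor use in expectation and keeps the type I error. Given a 15-point imbalance favouring indomethacin and d = 3, the one-sided error would be about 0.108, but that is conditional on an unlucky draw. Draws in the other direction offset it, and 0.05 holds overall.
- **The shifts are ordinary sampling error.** They are part of the standard error of 1.11, not an addition to it, and the table shows 95% extremes. One SD of imbalance gives 0.063 × 2 = 0.13 to 0.079 × 3 = 0.24 points for d = 2-3.
- **A difference of 2-3 points is large.** It is 40-60% of the assumed yearly decline of 5.0, and these are stable users analysed on change from baseline. Hence the range for d starts at zero.
- **The claim of balance in Section 8.** A reader might take "This procedure warrants a well-balanced initial randomization" as a promise about background treatment. The sentence that follows it concerns patient numbers per arm after withdrawals, so the claim is about arm sizes. Section 8 also does not say whether the list is blocked, so no conclusion about arm sizes during recruitment can be drawn.
- **An imbalance need not go unseen.** The five factors in 12.2 are not declared exhaustive, and the data are collected.
- **A separate analysis plan could add the factor.** That is true, and such a plan is not shown. But the protocol is not silent here: it names the comparison factors and the model terms and leaves this one out. Completing a stated analysis is a fair suggestion.

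**Conclusion.** The point holds as a modest improvement to a stated analysis, not as an error that threatens the trial. The protocol restricts a permitted background treatment in a way that implies an effect on cognition, yet it names neither a between-arm comparison nor a model term for it.

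The documents do not support a charge of bias, of type I error inflation or of faulty randomisation. What remains is chance imbalance left unadjusted, worth 0 to about 0.46 ADAS-cog points at the 95% extreme, and a standard error 0 to about 2.3% larger than need be. Both ranges rest on assumed values (20-50% users, 0-3 points) and on 80 per arm. If stable users and non-users decline at the same rate, both are zero.

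**What to change.** Before unblinding, make two additions:

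1. In Section 12.2, add cholinesterase-inhibitor use at baseline (yes/no) to the factors compared between arms.
2. In Section 12.3, add the same variable as a prespecified term in the ADAS-cog change model, to be kept whatever imbalance is observed.

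Medication is recorded at screening, so no new data, visits or patients are needed, and the randomisation list stays as it is. The change can be made whether or not enrolment has begun. The cost is one degree of freedom and a short amendment. Its main benefit is that any adjustment for this treatment is fixed in advance and not argued over after the results are known.

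### The primary model leaves out baseline ADAS-cog, which is already collected; the test stays valid but some precision is given up

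*Protocol*

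**What the plan says.** Section 12.2 (Stratification) states: "During the initial randomization there is no use for further stratification". For the final analysis it adds only that "the indomethacin and placebo group will be compared concerning age, sex, duration and severity of the disease (ADAS-cog score) and Apo E phenotype". It gives these factors no part in the treatment comparison.

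Section 12.3 (Statistical methods) names the primary analysis: a two-by-two analysis of variance of ADAS-cog change, with group and time as the factors. Secondary outcomes follow the same procedure. No section mentions a covariate.

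Section 12.1 (Sample size) assumes that "patients deteriorate 5.0 points (SD 7.0) on the ADAS-cog in one year" and that "a difference of 3.0 points or more regarding the changes from baseline is considered to be clinically relevant". It asks for "power of 80 percent", and "statistical testing will be done one-sided, at a significance level of 0.05". It concludes that "a total of 67 patients per group will be necessary", raised to 80 per group for 20% dropout.

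The evaluation schedule in Appendix II places ADAS-cog at baseline, week 26 and week 52. Section 5.3 adds: "Patients using stable doses of cholinesterase inhibitors were eligible", with the dose kept unchanged. Users and non-users can therefore both enter, but this factor is not in the list in section 12.2.

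**The concern.** Entry severity is wide (MMSE 10 to 26), there is no stratification, and the arms are small. The protocol regards baseline severity as worth comparing between the groups but attaches no consequence to the comparison. After a sound randomisation any baseline difference is due to chance, so comparing the groups neither reveals bias nor corrects the estimate. A covariate fixed in advance does correct it, and removes from the residual variance whatever it explains of the change.

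At stake is precision in a trial whose power is tight by its own figures. This is more than detail left to an analysis plan: section 12.3 names the model and its factors, and a later plan that added covariates would depart from it.

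**Working it through.** **Inputs from section 12.1.** Difference 3.0 points, SD of one-year change 7.0, one-sided level 0.05, power 80%, 80 per group, 20% dropout.

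**Input not in the protocol (assumption).** The correlation r between baseline ADAS-cog and one-year change, taken as 0.1 to 0.4 in size.

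**1. The protocol's own figure.** n per group = 2 × [7.0 × (1.645 + 0.842) / 3.0]² = 67.3. The stated 67 is reproduced apart from rounding. The trial is therefore sized on the unadjusted SD of change, which agrees with the unadjusted model in section 12.3.

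**2. Starting point.** 80 × (1 − 0.20) = 64 completers per arm. The standard error of the treatment difference is 7.0 × √(2/64) = 1.24 points. One-sided power from the noncentral t distribution is 77.8%.

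**3. With baseline ADAS-cog in the model.** Residual SD = 7.0 × √(1 − r²), again with 64 per arm:

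| r | Variance removed | Residual SD | One-sided power |
|---|---|---|---|
| 0 | 0% | 7.00 | 77.8% |
| 0.1 | 1% | 6.96 | 78.2% |
| 0.2 | 4% | 6.86 | 79.3% |
| 0.3 | 9% | 6.68 | 81.1% |
| 0.4 | 16% | 6.42 | 83.8% |

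Losing one degree of freedom out of 126 changes these powers by no more than about 0.01 percentage points.

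**4. Is the range reasonable?** If baseline and week-52 scores have equal variances and correlate at ρ, the correlation of baseline with change has size √[(1 − ρ)/2]. For ρ = 0.9, 0.8 and 0.7 this is 0.22, 0.32 and 0.39. These values of ρ are also assumptions, so they show only that the range is coherent.

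**5. Chance imbalance.** The standardised baseline difference has standard error √(2/80) = 0.158 at 80 per arm and √(2/64) = 0.177 at 64. It exceeds 0.2 SD in about 21% and 26% of randomisations. Such an imbalance moves the unadjusted estimate by 0.2 × r × 7.0 points: 0.14 at r = 0.1, 0.42 at r = 0.3 and 0.56 at r = 0.4. The standard error of 1.24 in step 2 already allows for this variation.

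**6. Cholinesterase-inhibitor use.** Suppose half the patients are users and decline differs by 1 to 3 points between users and non-users; neither figure is in the protocol. The variance explained is 0.25 × 1² / 49 = 0.5% to 0.25 × 3² / 49 = 4.6%. Adjusting for this factor alone takes power from 77.8% to between 78.0% and 79.5%.

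**The case against.** The best defence is that nothing here is wrong. An unadjusted comparison of change scores after randomisation holds its level, and the sample size rests on the same unadjusted SD. That stands. So does the remark that the 77.8% starting point arises from the dropout allowance (64 completers against the 67 required), which is a separate matter.

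Three stronger readings are tempting, and the protocol supports none of them.

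- A reader might infer that the primary estimate is biased, or that a baseline imbalance in ADAS-cog enters it in full. Chance imbalance is not systematic bias. The outcome is change, which already subtracts baseline, so only the part tied to r remains.
- A reader might infer that covariates will be chosen after the baseline comparison is seen. Section 12.2 says nothing of the kind and mentions no significance tests. Its wording leaves the purpose of the comparison open.
- A reader might infer that leaving out cholinesterase-inhibitor use is a serious gap. Step 6 shows a small effect even with generous inputs, and section 5.3 limits the variation by requiring stable, unchanged doses and barring new starts.

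It can also be said that covariates belong in the analysis plan. That would carry weight if section 12.3 were silent, but it lists the factors of the model and baseline is not among them.

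**Conclusion.** The point holds as a modest weakness in efficiency. Section 12.3 fixes a model without baseline ADAS-cog, and section 12.2 only compares baseline factors. At 64 per arm the power given up is 0.4 to 6.0 percentage points one-sided (77.8% against 78.2% to 83.8%), for an assumed correlation of 0.1 to 0.4 between baseline and change. At the low end the gain is negligible; at about 0.3 or above it brings power past the planned 80%. The size therefore depends on a figure that the protocol does not supply. The recommendation does not, because adjustment costs almost nothing. The calculation concerns change at one year, the quantity on which the trial was sized.

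**What to change.** - **Section 12.3, primary model.** State that the model for ADAS-cog change includes baseline ADAS-cog as a prespecified continuous covariate. Baseline cholinesterase-inhibitor use (yes/no) may be added; only a small gain should be expected from it.
- **Section 12.3, secondary scales.** Adjust for its own baseline each scale that has a scheduled baseline score and is not itself a rating of change: ADAS-noncog, MMSE and NPI. CIBIC+ is a rating of change and does not qualify. The IDDD row in Appendix II marks no visit, so IDDD qualifies only if a baseline assessment is scheduled.
- **Section 12.2.** Present age, sex, disease duration, severity and Apo E by group as a descriptive table, without tests, and state that it will not be used to choose covariates.

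The cost is one degree of freedom per covariate and the wording. For the primary model no new data are needed: ADAS-cog is scheduled at week 0 and medication is recorded at screening.
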